### Data management and protection

All study documentation at site will be held in restricted access areas and stored securely by study team members. Data will be entered by sites into a secure, validated online database (Elsevier MACRO v4) and accessible only by delegated team members of that site, and by delegated staff from the coordinating centre.

CRFs for the study will identify patients using a unique five-digit study identifier, year of birth and initials. Under the Data Protection Act 2018, the latter identifiers will be considered ‘personally identifying’ and will be treated as such by both the site team and coordinating centre team.

Where written communication (eg, data queries) on individual patient cases is necessitated between sites and the coordinating centre, only the study identifier should be used in the first instance.

Any transfer of documentation containing personally identifying data between site and coordinating centre will be subject to AES-256 industry-standard encryption.

### Statistical analysis

Summary statistics will be presented for each study phase (baseline, rapid local lab and central lab interventions) and each site, which will be percentages for binary outcomes such as whether transmission linkage for each HOCI was previously undetected. The frequency of IPC-defined HAIs, IPC-defined outbreak events and IPC with sequencing-defined outbreak events will be expressed as rate per week per 100 inpatients.

The outcomes of genotypic identification of transmission linkage not suspected at initial IPC investigation and impact of sequencing on IPC actions are only defined for the intervention periods. For such outcomes, the focus of analysis is to calculate summary statistics overall and for each site, which can be informally compared with the degree to which it is thought each site was able to fully implement the intervention. Variation over time within each site will also be explored, and the proportions will be compared between the rapid sequencing and delayed sequencing intervention periods.

The main analyses for the primary and secondary outcomes will be carried out on an intention-to-treat basis according to the defined study phases. However, sensitivity analyses will be conducted excluding study sites and/or periods with suboptimal implementation of the study intervention, both in terms of overall population sequencing coverage for HOCIs and the turnaround time for sequence reports being returned to IPC teams.

For outcomes defined in both the baseline and intervention periods, such as incidence of IPC-defined HAIs and the number IPC-defined hospital outbreaks, this can be informally compared between the baseline, intervention and (where implementation is justified) final control periods within sites. A formal analysis will be conducted based on negative binomial regression to detect the change in the incidence rate of each event type between baseline, intervention and control phases within site, including the current proportion of inpatients who are SARS-CoV-2 positive as a fixed effect and exposure ‘determined’ by the number of SARS-CoV-2-negative inpatients in that week. These analyses will also include adjustment for the proportion of HCWs at each site who have received at least one vaccine dose and a smoothed adjustment for calendar time. This will lead to an adjusted incidence rate ratio for the intervention effect, presented with a 95% CI.

Missing data will be identified, and efforts made to obtain the data. In the event that some sites are unable to implement the intervention fully during the intervention period then analysis will be repeated excluding such sites to provide a ‘per protocol’ analysis.

A detailed statistical analysis plan will be produced prior to commencement of analysis and agreed by the joint Trial Steering Committee and Data Monitoring Committee (TSC-DMC). All statistical tests will use a two-sided p value of 0.05, unless otherwise specified. All statistical analyses will be performed using Stata (StataCorp, College Station, Texas).

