## Methods and analysis

### Study design

COG-UK HOCI is a prospective, interventional, superiority clinical study, comprising three distinct phases with a possible fourth, dependant on interim data analysis.

In the first phase, all sites will collect baseline (non-interventional) eligible patient data for a period of 4 weeks to characterise each site’s usual practice in infection control in response to hospital-onset COVID-19 cases. This phase may include standard of care use of genome sequencing (eg, limited outbreak response analysis).

In the second and third phases, the study intervention will be applied on top of standard of care infection control practices.

The second phase requires ‘rapid’ turnaround of genome sequencing and sequence linkage report generation (ie, within 48 hours of first diagnostic SARS-CoV-2 PCR-positive result). This phase will be applied to all hospital onset COVID-19 cases meeting the eligibility criteria over an 8-week period.

The third phase is similar to the second, except that a 5–10 day turnaround time of genome sequencing and sequence report generation should be applied to mimic the use of a central sequencing laboratory. This phase will apply to all sites and last for 4 weeks.

The second and third phases may be applied in the reverse order at some sites, both for logistical reasons (ie, fine-tuning of rapid turnaround of whole-genome sequences) and also to ensure differences between sites in the calendar dates of each phase.

On review of interim analysis data, the study’s joint oversight committee may recommend a fourth phase for all sites comprising a second baseline period; this would be applied where the initial baseline data collection period occurred at a time of very high or low COVID-19 prevalence at the sites, whereby collecting data on standard practice could be unviable.

This will be a sequential study, with each National Health Service (NHS) Trust acting as its own control.

The total study duration per site will accordingly be 16–20 weeks, though it is likely that pauses in data collection will occur over the winter holiday break period due to most sequencing labs closing or moving to skeletal operations during this time.

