### Study outcomes

#### Primary outcomes

Incidence rate of PHE/IPC-defined SARS-CoV-2 HAIs (defined as SARS-CoV-2 cases with an interval of ≥8 days from admission to symptom onset, if known, or sample date), measured as incidence rate of recorded cases per week per 100 inpatients, during each phase of the study.Identification of linkage to individuals within an outbreak of SARS-CoV-2 nosocomial transmission using sequencing report data for HOCIs in whom this was not identified by presequencing IPC evaluation, for each enrolled patient during study phases in which the sequence reporting tool is in use.

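### HAI incidence is analysed by calendar phase with no transition period, so the early weeks of each phase largely reflect the preceding one, most of all in the 4-week slow phase

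*Protocol article*

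**What the plan says.** All places are in the protocol article.

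- **Primary outcomes.** An HAI is "defined as SARS-CoV-2 cases with an interval of ≥8 days from admission to symptom onset, if known, or sample date". Its incidence is "measured as incidence rate of recorded cases per week per 100 inpatients, during each phase of the study".
- **Study design.** At the start, "all sites will collect baseline (non-interventional) eligible patient data for a period of 4 weeks". The rapid phase follows for 8 weeks, with reports within 48 hours of the positive result. The slow phase lasts 4 weeks, and in it "a 5–10 day turnaround time of genome sequencing and sequence report generation should be applied to mimic the use of a central sequencing laboratory". A second 4-week baseline is optional. On order: "The second and third phases may be applied in the reverse order at some sites".
- **Statistical analysis.** On the analysis set: "The main analyses for the primary and secondary outcomes will be carried out on an intention-to-treat basis according to the defined study phases". The formal incidence model is a negative binomial regression on phase within site. It adjusts for the proportion of inpatients who are positive, staff vaccination and calendar time. Sensitivity analyses drop sites or periods with poor sequencing coverage or turnaround.

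The phases add up to 4 + 8 + 4 = 16 weeks, or 20 with the second baseline. That is exactly the stated study duration per site, so it contains no wash-in time. The pauses that the Study design section expects are for the winter holidays and are not tied to phase boundaries.

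**The concern.** A case counted early in a phase is mostly the product of events before that phase began. The 8-day rule guarantees that the patient was admitted under the preceding phase. A phase's own reports also cannot act from its first day: they first arrive up to 2 days after a positive result in the rapid phase and 5–10 days after in the slow phase. Any action taken on a report lowers the count only after a further interval from infection to detection. The Background calls the incubation period prolonged but gives no figure.

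Each phase's rate ratio is therefore a mixture of its own effect and that of the phase before. The slow phase is half as long and its reports start later, so a larger share of it is mixed. Late slow-phase reports also arrive in whatever phase follows, which could be a second baseline.

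At stake are the baseline-to-intervention rate ratios for HAIs and outbreaks, and any reading of how rapid and slow reporting differ on incidence. The footnote to the study schedule makes the second baseline depend on whether the first comparison leaves the benefit unclear. Dilution makes an unclear result more likely.

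**Working it through.** **The plan's own power figure.** Inputs from Sample size and power: 12 v 10 per week, variance 12, two-sided 5%, 14 sites. Power = Φ(δ/√(v/n₁ + v/n₂) − 1.96), with n in site-weeks.

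- 4 v 4 weeks (56 v 56): 2/√(12/56 + 12/56) = 3.055, power 86.3%. The article states 86.7%.
- 4 v 8 weeks (56 v 112): 2/√(12/56 + 12/112) = 3.528, power 94.2%.

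The stated figure thus fits equal 4-week periods. This is conservative for the rapid phase and not part of this point. The formula ignores covariates and overdispersion, and serves below only to compare options.

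**Share of a phase affected by an equal lag.** 8/28 = 28.6% of slow and 8/56 = 14.3% of rapid. With any equal lag the ratio is exactly 2.

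**Adding the report delay.** Assumed infection-to-detection lag: 5 days (range 3–7). Affected fraction f = (report delay + lag)/phase length.

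- Rapid: (2 + 5)/56 = 0.125; range 5/56 to 9/56 = 0.089 to 0.161.
- Slow: (7.5 + 5)/28 = 0.446; range 8/28 to 17/28 = 0.286 to 0.607.

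**Observed rate ratio v baseline.** Let the true ratio be 10/12.5 = 0.80 for both report types, from the plan's overdispersed power scenario. Observed = f × (ratio of preceding phase) + (1 − f) × 0.80.

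| Order | Rapid | Slow | Slow/rapid |
|---|---|---|---|
| Rapid first | 0.125 + 0.875 × 0.80 = 0.825 | 0.80 (follows rapid at 0.80) | 0.80/0.825 = 0.97 |
| Slow first | 0.80 (follows slow at 0.80) | 0.446 + 0.554 × 0.80 = 0.889 (0.857–0.921) | 0.889/0.80 = 1.11 (1.07–1.15) |

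The 0.97 assumes that the rapid effect persists until slow reports take hold. If counts instead returned to the baseline level for the 7.5 − 2 = 5.5 days by which slow reports start later, slow would be 5.5/28 + (22.5/28) × 0.80 = 0.839, and slow/rapid 1.02. The 0.97 is therefore the less firm figure.

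**Mix of orders.** ln 1.112 = 0.106 and ln 0.970 = −0.031. A simple average over sites is zero only if the slow-first share is 0.031/(0.031 + 0.106) = 0.23, about a quarter.

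**When the true effects differ.** Take true ratios of 0.833 (rapid) and 0.917 (slow), so rapid/slow is 0.909, with an equal 8-day lag. Rapid-first sites show 0.857/0.893 = 0.960, so the contrast shrinks. Slow-first sites show 0.845/0.940 = 0.899, so it is slightly exaggerated.

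**Power with and without a transition week**, for a phase that follows baseline and carries 7 days at the baseline rate:

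| Contrast | No carry-over | Carry-over left in | First week removed |
|---|---|---|---|
| Rapid v baseline | 94.2% | δ = 2 × 49/56 = 1.75: 87.0% | 4 v 7 weeks: 93.1% |
| Slow v baseline | 86.3% | δ = 2 × 21/28 = 1.5: 63.0% | 4 v 3 weeks: 80.7% |

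**The case against.** The strongest objection is that the article is silent on boundary cases and promises a detailed analysis plan, where lag coding usually sits. That would settle the matter if only detail were missing. But the article itself fixes weekly counting within phase and a main analysis by defined phase, and followed as written this puts the carry-over weeks into the phase effect. The planned sensitivity analyses do not reach them: a slow phase that returns reports on target at 5–10 days counts as well implemented. The listed covariates do not model a lag after a site's switch.

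Other objections narrow the point, and they stand.

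- A reader might infer that early-phase HAIs belong to the previous phase. Admission there is certain for about the first 8 days; infection there is only probable. The 29% and 14% are shares of time, not of bias.
- A reader might infer that both intervention effects are pulled toward the null. Only the phase that directly follows baseline is. In the default order, slow is pulled toward rapid.
- A reader might infer that the study's answer on time-criticality is distorted as a whole. The rapid-versus-slow comparison that is powered concerns the per-patient linkage proportion, which HAI carry-over does not touch. For incidence, power is given only for baseline v rapid, and no formal rapid-versus-slow test is named.
- The slow report delay is partly the intervention under test. Once reports flow, the delay shows as a weaker effect; the report-free start is the boundary artefact.
- Phase order is not purely a matter of logistics. Swapping is also meant to spread calendar dates across sites, and needs the sponsor's agreement.
- For the powered baseline-v-rapid contrast, the bias at rapid-first sites is small (0.80 to about 0.83) and conservative in a superiority study.

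**Conclusion.** The point holds in this limited form and is a cheap improvement. The by-phase analysis of HAI and outbreak incidence mixes each phase with the one before, and for an equal lag the slow phase is affected in twice the proportion of the rapid phase. A gap larger than twofold requires the longer report delay plus an assumed incubation.

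Under the stated assumptions, the diluted phase is rapid at rapid-first sites (about 0.83 instead of 0.80) and slow at slow-first sites (about 0.89, range 0.86–0.92). The resulting slow/rapid errors are about 3% one way and 11% the other. They are opposite in sign if the preceding effect persists through the switch, and cancel only in part, depending on a mix of orders that the article does not fix. The direction of pull, toward the preceding phase, is firmer than these sizes: the infection-to-detection lag and the equal true effects are assumptions.

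**What to change.** In the negative binomial model, code the first week of every phase after the first baseline (rapid, slow and any second baseline) as a separate transition level, so that it does not enter that phase's rate ratio. A lagged phase indicator would serve equally. Pre-specify a sensitivity analysis with a two-week transition for the slow phase, report it alongside, and also report the plain by-phase analysis.

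The two-week version is needed because one week does not cover the slow phase's 12.5 days. At slow-first sites 5.5 of the remaining 21 days would still be affected: 0.262 + 0.738 × 0.80 = 0.852, so slow/rapid is 1.065. Two weeks cover the central case. At the 17-day upper end, 3 of 14 days remain: 0.214 + 0.786 × 0.80 = 0.843, or 1.05.

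No new data are needed, since the model already works on weekly counts. The cost is precision, here by site-weeks:

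- Rapid v baseline, one week: √[(1/56 + 1/98)/(1/56 + 1/112)] = 1.02, a standard error about 2% larger.
- Slow v baseline, one week: √[(1/56 + 1/42)/(2/56)] = 1.08, about 8% larger.
- Slow v baseline, two weeks: √[(1/56 + 1/28)/(2/56)] = 1.22, about 22% larger. This is why it is better kept as a sensitivity analysis.

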### Health economic analysis

We will examine whether rapid SARS-CoV-2 genomic sequencing might lead to measurable economic advantages. A cost-benefit analysis will be conducted looking at the incremental cost or savings for the two sequencing approaches against baseline in the group of sites influenced by the time to sequence data result.

The cost of SARS-CoV-2 genome sequencing, generating the report and additional resources involved in teams training and review of the report, will be obtained from the participating laboratories and study sites.

HOCI resource use will be obtained from hospital records and CRFs supplemented with information obtained from members of the IPC teams at each site to inform IPC action-related cost. Costs will be evaluated from the NHS setting perspective over the study period. Economic benefits include the attributable cost savings from reducing the delay to initiate IPC measures to avert infection transmission, an estimate of the hospital cost savings due to excess bed days and days off work by HCWs.

Mean costs and SD for all phases of the study will be calculated. We will estimate the incremental mean difference in total costs between intervention phases and baseline of the study and 95% CIs.

Deterministic sensitivity analysis will be performed to assess the impact of varying resource use and other relevant parameters to identify variables with the highest impact on costs.

Adjustments will be made for variation in HOCI levels due to impact of B.1.1.7 variant of SARS-CoV-2 in the UK, as well as the national COVID-19 vaccine rollout.

A Health Economic Analysis Plan will be prepared for the study prior to commencing data analysis and will be approved by the TSC-DMC.

### Process evaluation

Process evaluations are now considered integral to understanding the factors which shape outcomes achieved within a study, enrich interpretation of findings and facilitate better understandings of how the intervention may be used in other settings to create sustainable health change.

The process evaluation embedded within the HOCI study aims to understand how the rapid genome-sequencing intervention works in practice across different sites.

The team will first develop initial programme theory for the SRT in advance of implementation. Programme theory describes the salient parts of the context in which the intervention will be implemented, the specific nature of the problem being addressed, the content or components of the intervention, the mechanisms through which the intervention works and how the intervention led to expected and unanticipated outcomes. Including the development of the programme theory as part of the study ensures that the team has derisked the intervention as far as possible by anticipating and mitigating potential problems or limiting factors.^12^

Data will then be gathered using a topic guide based on the programme theory. A purposive sample of HCWs involved in the chain of activity associated with implementing the SRT across five study sites will be interviewed. Interviews will take place during or soon after the rapid phase and focus on how the SRT and HOCI study more broadly have been implemented. A structured thematic analysis of the data will be conducted using the core elements of the initial programme theory, which will then be refined and used to share learning on HOCI and facilitate transferable knowledge and sustainable future healthcare.

### Study timelines

Sites will be opened using a staggered approach from October 2020 to January 2021 in order to provide the greatest likelihood of each phase of site activity covering peaks, troughs and moderate incidences of community prevalence and, therefore, likely hospital admissions of patients with COVID-19.

Patient recruitment at sites will run for 6 months from late October 2020 to end April 2021.

See table 1 for study schedule.

**Table 1 T1:** Study schedule

Timepoint (site dependent)	6 months	4 weeks	8 weeks	4 weeks	4 weeks	6 months
Study stage (site dependent)	Set up	First baseline/ control (daily)	Intervention sequencing result <48 hours (daily)*	Intervention sequencing result >4 days (daily)*	Second baseline/ control (where justified, daily)	Data cleaning, analysis and reporting
Site identification	X					
Site team discussion on sampling ability, staffing availability and logistics	X					
Initiation of contracts, R&D approvals	X					
NHS samples begin to be processed locally under COG-UK approvals (not study-related)	X					
NHS samples to be processed under COG-UK approvals, either locally or at Sanger		X	X	X	X	
Intervention reports generated			X	X		
Intervention reports returned to site ICTs (<48 hour)			X			
Intervention reports returned to site ICTs (>4 days)				X		
ICTs evaluate reports, seeking Expert Sequence Interpretation Team views if needed			X	X		
Case reports for HOCIs		X	X	X	X	
Process evaluation—qualitative interviews /analysis			X	X	X	x
Process evaluation—programme theory development and refinement	x		x	x	x	x
Interim analysis and views from TSC-DMC whether second baseline/control state acceptable					X†	
Data cleaning		X	X	X	X	X
Final data lock and analysis						X
Reporting/publication						X

*The order of ‘rapid’ phase (<48 hour turnaround time) and ‘slow’ phase may be swapped prior to commencement of either on agreement with the Sponsor. The option is offered to facilitate logistics/set-up at sites.

†TSC-DMC review should take place to determine whether it would be considered ethical to request sites have a second period of baseline/control (where sequencing data is not provided to IPC teams). This would only be on the basis that it is unclear from the initial baseline and intervention comparison whether there is a significant benefit; in cases where it is clear there is either benefit to the intervention or no benefit, then the second baseline would not take place.

COG-UK HOCI, COG-UK Consortium Hospital-Onset COVID-19 Infections; ICT, Infection Control Team; IPC, infection prevention and control; NHS, National Health Service; TSC-DMC, Trial Steering Committee and Data Monitoring Committee.

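### The trigger for the second baseline is stated in two different ways, and the version in the Table 1 footnote makes extra control data depend on the interim result with no error control stated

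*Protocol article*

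**What the plan says.** **Study design.** The joint oversight committee, after reviewing interim data, may recommend a fourth phase for all sites. The stated ground is prevalence: "this would be applied where the initial baseline data collection period occurred at a time of very high or low COVID-19 prevalence". The size or direction of the intervention effect is not mentioned.

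**Study timelines, Table 1, second footnote.** The committee is to judge whether it would be ethical to ask sites for another period without sequence reports. The condition is: "This would only be on the basis that it is unclear from the initial baseline and intervention comparison whether there is a significant benefit". The footnote adds: "in cases where it is clear there is either benefit to the intervention or no benefit, then the second baseline would not take place". Prevalence is not mentioned.

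**Statistical analysis.** The control period enters the formal model: "negative binomial regression to detect the change in the incidence rate of each event type between baseline, intervention and control phases within site". The significance level is general: "All statistical tests will use a two-sided p value of 0.05, unless otherwise specified". The article gives no interim boundary and no definition of a clear result.

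**Study monitoring** says only that the committee advises on the need for the fourth phase.

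**Dates.** "Patient recruitment at sites will run for 6 months from late October 2020 to end April 2021". Sites open in a staggered way from October 2020 to January 2021, and a site that runs all four phases needs 20 weeks.

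**The concern.** The two triggers give different answers in ordinary situations. If the first baseline fell at extreme prevalence and the interim comparison is clear, Study design supports a second baseline and the footnote rules it out. If prevalence was unremarkable and the comparison is unclear, the footnote allows it and Study design gives no ground for it.

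The footnote version also has a statistical consequence. Control time is added when the first comparison falls short and is not added when it succeeds. If both comparisons can be read at 0.05, the trial has two chances of a false positive, and the final incidence rate ratio and its 95% CI lose their nominal properties. The study is not randomised and each Trust is its own control, so the rule for adding control time bears directly on the incidence primary outcome.

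**Working it through.** **1. The triggers side by side**

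| First baseline | Interim comparison | Study design | Table 1 footnote |
|---|---|---|---|
| Extreme prevalence | Unclear | Run | May run |
| Extreme prevalence | Clear | Run | Do not run |
| Moderate prevalence | Unclear | No ground given | May run |
| Moderate prevalence | Clear | No ground given | Do not run |

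The two agree on running the phase only in the first row. They conflict in the second and diverge in the third.

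**2. Inputs**

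- 14 sites (Setting).
- First baseline 4 weeks: 14 × 4 = 56 site-weeks (Study design).
- Rapid phase 8 weeks: 112 site-weeks. Slow phase 4 weeks: rapid plus slow = 168 site-weeks (Study design).
- Second baseline 4 weeks: control total rises to 112 site-weeks (Table 1).
- Two-sided 0.05 (Statistical analysis).

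**3. The plan's own figure**

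The article states no type I error for a two-look procedure. Its nearest figure is 86.7% power for a fall from 12 to 10 per week with variance 12 (Sample size and power). With 56 v 56 site-weeks, SE = √(12 × (1/56 + 1/56)) = 0.655, 2/0.655 = 3.055, and power = Φ(3.055 − 1.96) = 86.3%, close to the stated value. With the planned 56 v 112, SE = 0.567 and power is 94.2%. The stated figure therefore matches equal phase lengths. The steps below use the phase lengths in Study design.

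**4. Correlation of the two looks**

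Let Z1 compare intervention with the first baseline, and Z2 compare intervention with both baselines. Under the null they are bivariate normal with correlation √(var2/var1). A common overdispersion factor cancels.

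- Rapid phase only, in weeks per site: var1 ∝ 1/4 + 1/8 = 0.375; var2 ∝ 1/8 + 1/8 = 0.25; correlation = √(0.25/0.375) = 0.816.
- Rapid plus slow: var1 ∝ 1/4 + 1/12 = 0.333; var2 ∝ 1/8 + 1/12 = 0.208; correlation = 0.791.

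**5. Overall two-sided type I error by the meaning of a clear result**

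The final test is at 0.05 throughout. The first row is exact, from the bivariate normal; the next two are simulated.

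| Rule at the first look | Rapid only | Rapid + slow |
|---|---|---|
| Clear = p<0.05 in either direction; otherwise extend | 7.7% | 7.9% |
| Clear benefit z>1.96; no-benefit stop if z is below a cut-off between 0 and 1.28 | 6.0-6.4% | 5.9-6.4% |
| Clear benefit z>2.576 to 3.29; same no-benefit cut-offs | 4.6-5.1% | 4.5-5.2% |
| Trigger independent of the comparison | 5.0% | 5.0% |

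In the second row the false-benefit tail is about 3.4-3.9% instead of 2.5%.

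**6. Equal critical value that restores 5%**

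Solving P(|Z1|>c or |Z2|>c) = 0.05 gives c = 2.147 (p = 0.032) for the rapid phase only, and c = 2.156 (p = 0.031) with rapid and slow pooled.

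**7. Calendar**

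Four phases take 4 + 8 + 4 + 4 = 20 weeks = 140 days. 30 April 2021 minus 140 days is 11 December 2020. Even the three-phase course of 16 weeks (112 days) requires opening by 8 January 2021, before any allowance for the winter pauses that Study design expects.

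**The case against.** The strongest reply is that the two statements answer different questions. Study design says why a second baseline might be needed. The footnote says when withholding reports would still be ethical, and its *only* sets a necessary condition. Need plus permission can work together, and both decisions lie with the same committee. This stands in part: a reader might infer that the two rules cannot both hold, and that goes too far. But neither place states the joint reading, so the article leaves the operating rule open.

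The second reply is that two tests at 0.05 is an assumption. The footnote does not define *clear*, does not name the outcome compared, and does not say that a first-look result would be declared as the trial's finding. The 0.05 level applies unless otherwise specified, and a separate analysis plan may set a boundary. This also stands in part. A reader might infer a flat inflation to more than 7%, but that needs *clear* to mean p<0.05 with continuation in both directions. The footnote speaks of benefit or no benefit, which fits a one-directional stop at least as well, and a strict boundary for benefit removes the inflation. Still, an analysis plan would not by itself cure the differing triggers.

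The third reply is that the footnote is an ethical safeguard. That is a fair reason not to delete it outright, but it does not remove the statistical effect of a result-dependent extension.

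On the calendar, the fourth phase is only a possibility, and Table 1 marks it as site dependent and where justified. Study design nonetheless frames it as for all sites, which the dates do not allow.

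**Conclusion.** The point holds in a limited form. The trigger is stated differently in two places, and they can be reconciled only by a joint reading that neither gives. The footnote makes further control data depend on a look at the result, and those data enter the final model with 0.05 as the only stated level.

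The overall two-sided type I error lies at about 5-8%, with 7.7% (7.9% with rapid and slow pooled) at the upper end. Where it falls depends on a definition that the article does not give.

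These figures assume that HAI incidence is the outcome compared. That is an inference: it is the only primary outcome defined in the baseline phase. They also assume independent weeks of equal variance, a first look at complete phase data from all sites, and no adjustment for calendar time, prevalence or vaccination. The planned model includes those adjustments, so the correlation between looks could differ. The second primary outcome, previously unidentified linkage, is defined only in the intervention phases and is not affected.

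The calendar conflict is plain arithmetic: sites opened after 11 December 2020 cannot complete four phases by the stated close of recruitment.

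**What to change.** Reconcile Study design and the Table 1 footnote into one rule, worded identically in both places. There are two coherent options.

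- **Prevalence only.** The committee decides on prevalence during the first baseline, without sight of the baseline-v-intervention HAI comparison. The type I error stays at 5%, and the cost is wording plus a line in the committee charter.
- **Prevalence with the equipoise check kept.** State that both conditions apply, name the outcome reviewed, and define clear benefit and clear absence of benefit in advance. Use a strict interim boundary or a spending function; if both looks are tested equally, about p<0.032 at each (0.031 with rapid and slow pooled). The cost is a small loss of power.

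In either case, limit the second baseline to sites that can complete it before recruitment closes, or move the closing date, and amend the reference to all sites to match.
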